**Methodology**

**1 Study setting:** From August 2022 to Match 2023, patients will be screened and recruited by the Department of Neurological Rehabilitation and Neurology in the Seven People’s Hospital of Shanghai via reviewing their electronic medical records.

**2 Eligibility criteria**

**2.1 Inclusion criteria**

1. Presence of stroke documented by CT or MRI, including ischemic and hemorrhagic stroke;
2. Subacute stage of stroke (first onset, duration of disease within 6 months);
3. Ability to sit and balance without upper limb support, and able to tolerate at least half an hour of training or testing;
4. Brunnstrom classification of the patient's upper limb is ≤4;
5. Stable blood pressure (less than 160/100 mmHg);
6. Good cognitive ability (Mini-Mental State Examinatione score ≥22)^[43]^;
7. Good muscle tone (modified Ashworth classification < level 2);
8. No severe visual impairment or visual field defect;
9. Age between 35-80 years old, with no gender limit.

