**Background**

Stroke is an acute cerebrovascular disease caused by the sudden rupture or occlusion of blood vessels. It is divided into two main types: ischemic stroke, which accounts for 87% of cases, and hemorrhagic stroke, which accounts for 13%^[1]^. Ischemic stroke occurs when there is ischemia and hypoxia in the brain tissue around the blood vessel supply area, leading to a disruption of local blood supply and resulting in neurological deficits^[2]^. Hemorrhagic stroke is characterized by spontaneous intracranial hemorrhage, including cerebral hemorrhage and subarachnoid hemorrhage. It is typically caused by arterial rupture due to non-traumatic factors^[3, 4]^. Stroke is the second most common cause of death and the leading cause of disability worldwide^[5, 6]^. According to statistics from the World Health Organization, approximately 15 million people worldwide suffer from stroke every year. Out of these, more than 5 million people die from stroke and another 5 million people experience permanent severe disabilities^[7]^. Moreover, stroke often leads to severe complications in patients, including neuropsychiatric disorders and impairment of motor, sensory, and cognitive abilities^[8, 9]^. Among long-term stroke survivors, 70%-80% of patients will have various types of functional impairments^[10]^. This includes 48% with hemiplegia^[11]^, 22% who are unable to walk, and 24%-53% who are partially or completely dependent on daily life activities^[12]^. Additionally, 55-75% of them still experience upper limb dysfunction 3-6 months after the stroke onset^[13]^. This dysfunction is characterized by abnormal postures such as scapula withdrawal and sinking, shoulder joint flexion, adduction, internal rotation, elbow joint flexion, forearm supination, finger flexion, etc. Furthermore, 37% of patients have varying degrees of upper limb fine motor impairment^[14]^. Unilateral upper limb dyskinesia is a frequently observed complication^[15, 16]^. Individuals experiencing upper limb dysfunction often exhibit restricted joint movement, muscle contraction difficulties, and coordination disorders^[17]^. Following a stroke, upper limb dysfunction can greatly impede daily activities like eating, dressing, and washing^[18, 19]^. This limitation increases patients' reliance on others and negatively impacts their long-term quality of life^[20]^. Consequently, rehabilitating upper limb dysfunction becomes imperative in enhancing their functional capabilities.

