**2.2 Exclusion criteria**

1. Presence of severe bone and joint disease, muscle disease, or other neurological diseases, or a history of upper limb surgery;
2. History of skull fracture and/or severe head injury; presence of aphasia, hearing impairment, or other communication difficulties that hinder normal communication with others;
3. Manifestation of obvious shoulder pain, with a pain score at rest exceeding 5^[44]^;
4. Duration of the disease exceeding 6 months since onset;
5. Severe visual or hearing impairment that hampers the ability to cooperate with training;
6. Coexistence of severe liver, kidney, heart, lung, and blood disorders, as well as other systemic diseases;
7. Participation in other ongoing clinical studies.

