**4 Randomized grouping and allocation concealment**

In this study, a total of 93 subjects will be evenly divided into 3 groups, with 31 cases in each group. The groups will be named as follows: BWS-TCY group, CRT group, and RAT group. Subject randomization will be performed by an external professional statistician. After baseline testing, each participant received an envelope containing a randomly assigned serial number to determine their group. The random sequence will be generated by an independent professional statistician using SPSS software (IBM Corp., IBM SPSS Statistics, V25, Armonk, NY, USA), with the random number seed set to 20210608. Throughout this process, the statisticians, outcome assessors, and data analysts will be blinded to the study's recruitment, intervention, and evaluation. The randomization assignments ill be placed in sealed opaque envelopes by an independent researcher who will be also blinded to the trial. The identity of each participant is represented by a serial number, which is numbered according to their entry into the group. The letters 'A', 'B', and 'C' are used to represent the assigned groups, with 'A' corresponding to the BWS-TCY group, 'B' to the CRT group, and 'C' to the RAT group. The randomization process will be conducted by an independent researcher. Three rehabilitation therapists will be responsible for recruiting and assigning participants to conduct the intervention. Due to significant differences between the groups, neither the researchers nor the therapists will be blinded. The study will be designated as open-label, so the patients will be not blinded.

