**8 Statistical method**

The clinical data will follow the per-protocol (PP) analysis and intention-to-treat (ITT) analysis. PP analysis was applied to all the randomized participants who will not stop treatment prematurely, and complete 4 weeks of treatment. ITT analysis is applied for participants who have dropped out of the trial, according to the rule of last-observation-carried-forward. The normality test of the measurement data is performed using the Shapiro-Wilk method, and the conformity distribution is expressed as the mean ± standard deviation. P<0.05 is significant for the difference. Categorical data, such as gender or those expressed as frequencies (%) will be analyzed using the chi-square test or Fisher’s exact test. Perform nonparametric statistical tests on data that do not conform to the normal distribution. In addition, statistically significant differences in intra-group and inter-group data will be analyzed by repeated measurements of ANOVA. All statistical analysis will be performed using IBM SPSS version 25.0 (SPSS Inc., Chicago, IL, USA). Missing data patterns will be analyzed by missing value analysis.

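### Time since stroke is neither balanced nor modelled, so avoidable variance stays in the FMA-UE comparison (a modest loss of precision, not a bias)

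*Protocol*

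**What the plan says.** Entry is limited on one side only. Section 2.1 requires "Subacute stage of stroke (first onset, duration of disease within 6 months" and section 2.2 excludes "Duration of the disease exceeding 6 months since onset". Neither gives a minimum number of days. Very early entry is restricted indirectly, by the word subacute and by the requirement of "Ability to sit and balance without upper limb support, and able to tolerate at least half an hour of training or testing".

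Section 4 describes the allocation in some detail: "The random sequence will be generated by an independent professional statistician using SPSS software", with a fixed seed, sealed envelopes and letter codes for the arms. On balance it says only that "a total of 93 subjects will be evenly divided into 3 groups, with 31 cases in each group". It names no stratification factor, block or minimisation.

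Section 8 states that "statistically significant differences in intra-group and inter-group data will be analyzed by repeated measurements of ANOVA". No covariate is named.

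The Background bases the trial's rationale on early treatment. It cites a guideline for the view that starting rehabilitation sooner gives better results.

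**The concern.** Patients in their first weeks after stroke and patients close to six months can be expected to gain different amounts on FMA-UE over the same treatment period, whichever arm they are in. The protocol itself regards timing as relevant, yet uses it only as an eligibility limit.

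Baseline FMA-UE, as the first repeated measure, takes out differences in starting level. It does not take out differences in recovery rate between patients who start at the same level.

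Two things are at stake. Variation explained by onset time stays in the error term and lowers power. And if one arm happens to hold clearly more early patients, readers will ask how much of the difference that explains, and the stated analysis has no prespecified answer.

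**Working it through.** **Inputs from Protocol section 3.** Pilot FMA-UE after 4 weeks: 35.5 (SD 9.5) for BWS-TCY, 34.28 (9.58) for RAT and 29.00 (10.2) for CRT, from 15 patients in total. Evaluable total 84, so 28 per arm; 93 with dropout, so 31 per arm. Two-sided alpha 0.05, power 80%.

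**Assumption.** The documents give no correlation r between time since onset and the analysed FMA-UE outcome. I use r = 0.2 to 0.5.

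**The plan's own figure.** Pooled SD = sqrt((9.5² + 9.58² + 10.2²)/3) = 9.77. The SD of the three means is 2.82, so Cohen's f = 2.82/9.77 = 0.289. A one-way ANOVA with this f needs 120 patients. A repeated-measures between-group test gives exactly 84 with four measurements and a within-patient correlation of 0.6. The protocol states neither setting, so 84 can be reached but not confirmed. For dropout, 84 × 1.1 = 92.4, rounded up to 93.

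**How far the arms may differ by chance (31 per arm).**
- If onset time were uniform over 0–180 days (assumption), its SD is 180/sqrt(12) = 52 days. The difference in arm means has SE 52 × sqrt(2/31) = 13 days, a 95% range of about ±26 days.
- If half the patients are early, the difference in the early share has SE sqrt(0.25 × 2/31) = 12.7 percentage points, a 95% range of about ±25 points.
- The resulting shift in the FMA-UE difference has SD r × 9.77 × sqrt(2/31). Its 95% range is ±1.0 points at r = 0.2 and ±2.4 at r = 0.5.
- The full standard error of the difference is 9.77 × sqrt(2/31) = 2.48 points, a 95% range of ±4.9. The chance shift is part of this standard error, not an addition to it.

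**Type I error.** In simulation (8,000 trials per scenario, 28 per arm, no true difference), the unadjusted three-arm test rejected in 5.1% of trials at r = 0.3 and 5.2% at r = 0.5. The adjusted test rejected in 5.1% and 4.9%.

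**Gain from adjustment (28 per arm).** Adjusted SD = 9.77 × sqrt(1 − r²); SE = SD × sqrt(2/28). Power is from the noncentral t distribution, with 54 degrees of freedom unadjusted and 53 adjusted.

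| r | SD | SE | Power, 6.5 points (35.5 − 29.00) | Power, 1.22 points (35.5 − 34.28) |
|---|---|---|---|---|
| no adjustment | 9.77 | 2.61 | 68.7% | 7.5% |
| 0.2 | 9.57 | 2.56 | 70.4% | 7.6% |
| 0.3 | 9.32 | 2.49 | 72.7% | 7.7% |
| 0.5 | 8.46 | 2.26 | 80.6% | 8.3% |

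Simulated power of the three-arm test rises from about 63% to 67% at r = 0.3 and to 76% at r = 0.5.

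**Is the assumed range plausible?** As a rough check, let entry be uniform over weeks 2–26 and natural gain be A × (exp(−t/τ) − exp(−(t+w)/τ)), with (A, τ) = (20, 6), (25, 8) and (15, 10). All of these values are assumptions. Natural recovery then explains 1–4% of the sampling variance for w = 4 weeks and 5–16% for w = 12 weeks. The square roots correspond to r of about 0.1–0.2 and 0.2–0.4. The lower part of the range is therefore the more realistic on the SD of scores. The share would be larger against a smaller SD of change, which the protocol does not give.

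**The case against.** The strongest reply is that randomisation already deals with this. The variation sits in the outcome SD and hence in the standard error, so leaving out the factor neither biases the comparison nor raises the false-positive rate. That stands in full. Covariates are also commonly named in an analysis plan, which is not shown here. That stands too, but section 8 does specify a model, and the allocation method of section 4 cannot be mended after enrolment. Finally, stratifying 93 patients at one centre on this factor rather than another is a design preference. That is fair, and is why stratification is only optional below.

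Four stronger readings are tempting, and the documents do not support them.
- From the missing lower limit, a reader might infer that patients enter immediately after stroke. The subacute label and the sitting and tolerance requirements speak against that.
- From the Background's statement that "55-75% of them still experience upper limb dysfunction 3-6 months after the stroke onset", a reader might take the complement as a recovery rate. The sentence does not say that all of these survivors had the dysfunction at onset, and it does not describe the trial's population.
- A reader might conclude that imbalance could by itself produce the arm difference sought. For the 6.5-point contrast with CRT, the probability of a chance shift that large is below 0.002% even at r = 0.6.
- A reader might compare 12 weeks of natural recovery with the 1.22-point BWS-TCY versus RAT difference. That difference was observed at 4 weeks. With a 4-week gain in the recovery model above, the chance difference between two arms exceeds 1.22 points in only 0–1.5% of randomisations. The protocol gives both 4 and 12 weeks as the treatment period, which needs reconciling, but it offers no 12-week difference for comparison.

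**Conclusion.** The point holds as one about precision and interpretability. A baseline variable that the protocol itself treats as relevant, and that must be known for every patient, is used neither in the allocation nor in the stated model. The comparison stays valid.

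The expected gain from adjustment is modest: for the 6.5-point contrast with CRT, power rises from about 69% to 70–73% at r = 0.2–0.3, and to about 81% at r = 0.5. There is no material gain for BWS-TCY versus RAT. That contrast is limited by sample size, not by time since onset.

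The result rests on an assumed correlation and on SDs from a 15-patient pilot, measured on 4-week scores rather than on change.

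**What to change.** In section 8, name time since onset as a prespecified baseline covariate in the FMA-UE between-arm comparison. In a repeated-measures model it should enter with its interaction with visit, so that it can account for differences in recovery and not only in level. The cost is one model term and no new data.

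Optionally, in section 4, stratify the allocation list by time since onset, for example up to 3 months versus over 3 months, with blocks of varying size within each stratum. The independent statistician then prepares two lists, and arm sizes may differ slightly from 31. Neither change needs extra patients, visits or measurements.

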**2.2 Exclusion criteria**

1. Presence of severe bone and joint disease, muscle disease, or other neurological diseases, or a history of upper limb surgery;
2. History of skull fracture and/or severe head injury; presence of aphasia, hearing impairment, or other communication difficulties that hinder normal communication with others;
3. Manifestation of obvious shoulder pain, with a pain score at rest exceeding 5^[44]^;
4. Duration of the disease exceeding 6 months since onset;
5. Severe visual or hearing impairment that hampers the ability to cooperate with training;
6. Coexistence of severe liver, kidney, heart, lung, and blood disorders, as well as other systemic diseases;
7. Participation in other ongoing clinical studies.

**2.3 Elimination and discontinuation criteria**

1. Patients who provided incomplete information, leading to missing data on the main outcome indicators;
2. Patients who provided false information;
3. Patients with other systemic diseases that made them unsuitable to continue participating in the study;
4. Patients who experienced sudden illness or adverse events during the trial intervention period and were unable to continue or participate in the training;
5. Participants who voluntarily withdrew from the study;
6. Participants who experienced adverse events.

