**6 Interventions**

All patients will receive rehabilitation intervention in addition to routine medical treatment and daily care in the hospital. The patient's safety status will be continuously recorded throughout the intervention. The rehabilitation intervention will last for 12 weeks, with sessions of 60 minutes per day, 5 days per week.

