**Duration of the project**

12 weeks intervention and 12 weeks follow-up.

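### Section 2.3 merges elimination with discontinuation, and its item 6 catches any participant with any adverse event; the item should be deleted or limited, and the list's effect on the analysis sets stated

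*Protocol*

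**What the plan says.** Section 2.3 of the protocol, Elimination and discontinuation criteria, has six items under one heading. None is assigned to either action. Three matter here:

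- Item 1: "Patients who provided incomplete information, leading to missing data on the main outcome indicators".
- Item 4: "Patients who experienced sudden illness or adverse events during the trial intervention period and were unable to continue or participate in the training".
- Item 6: "Participants who experienced adverse events".

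The Quality assurance section defines an adverse event as any untoward medical occurrence at any time in the study, with cardiovascular events, cerebrovascular events and falls as examples. Oversight and monitoring says that such events are recorded on the case report form, assessed, treated and managed. It does not mention removing the patient.

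Section 8 names two analyses. For per-protocol: "PP analysis was applied to all the randomized participants who will not stop treatment prematurely, and complete 4 weeks of treatment". For intention-to-treat: "ITT analysis is applied for participants who have dropped out of the trial, according to the rule of last-observation-carried-forward". Neither definition refers to section 2.3.

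On blinding, section 4 says that "the statisticians, outcome assessors, and data analysts will be blinded", and that researchers, therapists and patients are not. The Follow-up section plans 12 weeks of follow-up after the intervention for everyone.

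**The concern.** A criterion that acts after randomisation is safe only if it is clear what it does and if it is not triggered by something the treatment can influence. Item 6 fails on both counts. It does not say whether the patient stops training, stops being assessed or leaves the analysis. Its trigger is an adverse event of any kind, and the arms differ in what could cause one: two use a robot and one does not.

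If staff apply the item literally, a patient with a minor event who is able and willing to carry on is stopped or removed. If that happens more often in one arm, the groups compared at the end are no longer the groups that were randomised. The people who see the events and run the sessions know the allocation, so judgement about what counts as an event may also differ by arm.

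Item 1 raises a related question. Patients with a missing primary outcome are among those whom an intention-to-treat rule with last observation carried forward is meant to keep. If item 1 removes them from that analysis, the two sections work against each other.

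**Working it through.** The point disputes no figure in the protocol, so the check is a side-by-side reading.

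**Step 1: what item 6 adds to item 4.** Item 4 has three conditions: a sudden illness or adverse event, timing within the intervention period, and inability to go on with training. Item 6 keeps only the adverse event. Every adverse event case under item 4 is therefore also a case under item 6. What item 6 adds is exactly the group that item 4 leaves out: patients with an event who can continue, and patients whose event falls outside the intervention period. For the second group no training is left to stop, so the item could only end follow-up or remove data.

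**Step 2: how wide the trigger is.** The Quality assurance definition has no threshold of severity or relatedness. A harmless fall qualifies. No other section narrows the term for the purpose of section 2.3.

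**Step 3: what follows under each meaning of item 6.**

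| Meaning | Consequence |
|---|---|
| Removed from all analyses | A post-randomisation exclusion that depends on an event which may differ by arm; it contradicts the intention-to-treat analysis in section 8 |
| Removed from the per-protocol set only | No conflict with intention-to-treat, but the per-protocol set is selected on an event that may differ by arm |
| Training stopped, assessments continue | An unnecessary stop for a patient able to train; one who stops within the first 4 weeks fails the per-protocol definition |
| Training and assessments both stopped | The same stop, and later scores are replaced by an earlier value carried forward although they could have been measured |

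None of the four is desirable for a patient who is able to continue, and the protocol does not choose between them.

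**Step 4: whether blinding helps.** Section 4 blinds statisticians, assessors and analysts. That protects the scoring and the analysis. It does not help if the trigger itself has a different frequency by arm, because a blinded analyst would apply the same rule and remove more patients from one arm.

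**Step 5: item 1 against section 8.** If item 1 affects only the per-protocol set, it agrees with section 8. If it reaches the intention-to-treat set, it removes patients whom the carry-forward rule keeps. Section 8 does not refer to section 2.3 and section 2.3 does not name a set, so the text supports either reading.

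**Step 6: what the numbers allow.** Section 3 plans 84 patients plus a 10% dropout allowance, giving 93 (84 × 1.1 = 92.4, rounded up). The margin is 93 − 84 = 9 patients, or 3 per arm, for losses of every kind. The protocol gives no adverse event rate and no outcomes for affected patients. How many patients item 6 would take, and in which direction the comparison would move, cannot be calculated from it.

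**The case against.** The strongest reply is that item 6 is a loose repeat of item 4. Section 2 repeats itself elsewhere: the exclusion for disease beyond 6 months restates an inclusion criterion. A discontinuation criterion that acts when no training is left also looks more like a slip than a plan. This may well be what the authors intended. It does not answer the point, because staff apply the written text and nothing narrows it. If the item is a repeat, deleting it loses nothing.

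The second reply is that section 8 governs the analysis sets, keeps dropouts by carrying values forward, and plans to examine missing-data patterns, which presupposes that patients with missing values stay in the data. Follow-up is also planned for all participants, and Oversight and monitoring deals with adverse events without mentioning removal. Much of this stands. A reader might infer that item 1 flatly contradicts the intention-to-treat rule, or that the protocol prescribes a biased primary analysis. The documents do not support either: the conflict exists on one reading only, and sections 8 and Follow-up lean towards keeping patients.

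The third reply is that a link between criteria and analysis sets can wait for a statistical analysis plan. For item 1 alone that would carry weight. Item 6 is different, because it is a stated rule applied by staff during the trial, and a later plan cannot recover assessments that were never made.

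A reader might also infer that harms would be hidden. They would not, since adverse events are recorded whatever happens to the patient.

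**Conclusion.** The concern holds in a limited form. Item 6 is a badly fixed rule: as written it stops or removes randomised patients for any adverse event, adds to item 4 only patients who should not be stopped or removed, and rests on an event that may differ by arm where therapists and patients are unblinded. The merged heading leaves its effect undefined. Item 1 is a conditional problem: it conflicts with section 8 only if it reaches the intention-to-treat set.

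No size is attached. That the arms differ in adverse event frequency is a possibility, not something the protocol reports.

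A reader might infer a loss of power from the margin of 9 patients. The documents do not support a figure. Patients kept under intention-to-treat do not leave the analysis, and any power curve depends on an effect size that the protocol does not settle. The pilot means and standard deviations in section 3 give f = 2.821 / 9.765 = 0.289 (standard deviation of the three means over the pooled standard deviation). A simple one-way three-group test then has about 64% power at 84 patients, whereas the stated 80% would need f of about 0.345 in that test.

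A reader might also want to count study weeks covered by each item, or ask about patients who stop after week 4. Both depend on whether the intervention lasts 4 weeks (Study design) or 12 ("The rehabilitation intervention will last for 12 weeks, with sessions of 60 minutes per day, 5 days per week"). That is a separate matter and adds no weight here.

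**What to change.** Change section 2.3 in two ways.

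1. Delete item 6, or limit it to adverse events that make continued training unsafe.
2. Add a short statement on what the list does, for example: *The criteria in this section stop training or affect only the per-protocol set. Every randomised patient stays in the intention-to-treat analysis under the missing-data rule in section 8. Planned assessments continue after training stops unless the patient withdraws consent.*

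The second change also settles item 1, since missing main-outcome data would then be handled by section 8 and could affect only the per-protocol set.

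The cost is protocol wording. No sample-size figure changes. The downside is that patients who stop training still attend assessments, which the Follow-up section already plans for all participants.
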